**OBJECTIVE:**

To evaluate the efficacy and safety of acupuncture treatment for residual insomnia and other residual symptoms associated with major depressive disorder

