**CLINICAL EFFICACY VARIABLES:**

Primary outcomes measures are sleep parameters measured by actigraphy, Insomnia Severity Index (ISI) and sleep log, and depressive state as measured by Hamilton Depression Rating Scale (HDRS). Secondary outcomes are Pittsburgh Sleep Quality Index (PSQI) and Sheehan Disability Index (SDI).

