**Plan of Investigation**

*Study Design*

The proposed study is a randomized, prospective, placebo-controlled, single-blind trial of electroacupuncture for residual insomnia associated with MDD. The study design aims to differentiate three plausible mechanisms for sleep improvement in patients with insomnia symptoms: (1) needling at specific sites based on traditional Chinese medicine (TCM) theory; (2) characteristic and incidental elements of acupuncture treatment, e.g. credibility of intervention, patient expectations;13 and (3) underlying fluctuations in the disorder, regression to the mean, or non-specific improvement associated with participating in a clinical trial.

Eligible patients will be randomized in a ratio of 1:1:1 to: (1) traditional electroacupuncture; (2) placebo acupuncture using Streitberger needle; and (3) waiting list control group. Active or placebo acupuncture treatment will be given 3 sessions per week for 3 weeks. Patients in the waiting list control group will not receive any treatment for a period of 8 weeks after randomization. After that time, they will receive the same treatment as in the traditional electroacupuncture group. The subjects’ sleep and residual symptoms will be assessed at baseline, after completing 2 weeks of acupuncture treatment, and at 1-week, 5-week and 13-week posttreatment.

*Subjects*

Outpatients, aged from 18 to 65 years, with a previous DSM-IV MDD and a chief complaint of insomnia will be invited to participate in this study. Written informed consent would be obtained prior to study procedure. Subjects would be excluded if they: (1) have a Hamilton Depression Rating Scale scores above 18; (2) have sleep apnea or periodic limbs movement disorder detected by overnight polysomnography; (3) have suicidal risk; (4) have previous history of schizophrenia, other psychotic disorders, and bipolar disorder; (5) are pregnant, breast-feeding, or woman of childbearing potential not using adequate contraception; (6) have infection or abscess close to the site of selected acupoints and in the investigator’s opinion inclusion is unsafe; and (7) are taking Chinese herbal medicine or over-the-counter drugs which are intending for insomnia.

The number of subjects to be recruited in each treatment group would be 30.

*Treatment Protocol*

Traditional Acupuncture

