The subjects will receive the Structured Clinical Interview for DSM-IV to evaluate psychiatric diagnoses and polysomnography to exclude specific sleep disorders prior to randomization. Block randomization is used in the randomization procedure. This is performed by using Excel to generate a randomized block list.16 Subjects are randomly assigned to one of the three groups after baseline visit.

Method of blinding

The subjects are told as follows “This study is to evaluate the therapeutic effects of acupuncture on treating insomnia in depressive patients. You will be randomly assigned to traditional acupuncture group for insomnia or acupuncture-like placebo treatment group”; “Traditional acupuncture is an acupuncture treatment that conventionally used in Chinese medicine practice; placebo acupuncture is a procedure which mimics the real acupuncture procedure and give you a perception that you are receiving the acupuncture treatment”. The researchers who analyse the data will be blind to the treatment allocation.

Concomitant Therapy

Antidepressants will be maintained the same dosage during the study period. Sedatives, hypnotics or anxiolytics are allowed during the study. The subjects are told to record their dosage of these medications. Drug counts will be conducted at each study visit. Individual psychotherapy should be maintained if it is ongoing prior to the study. Any new form of therapy or education is disallowed.

*Outcome Assessment*

Subjective assessment

1. Insomnia Severity Index (ISI) (Primary outcome measure)

ISI is a 7-item self-rating scale. The subjects rate their severity of sleep problem and the daytime function performance due to insomnia using a 5-point Likert scale.

2. Sleep log

The subjects record their daily sleep-wake schedule on a standardized sleep log.

3. Hamilton Depression Rating Scale (HDRS)

HDRS is a 21-item scale which the clinicians used to rate the severity of patients’ depression. HDRS rates the severity of other depressive symptoms such as low mood, insomnia, agitation, anxiety and weight-loss.

4. Pittsburgh Sleep Quality Index (PSQI)

PSQI is a self-rating scale that assesses the subjects’ sleep in the past month. It has seven components, namely subjective sleep quality, sleep latency, sleep duration, habitual sleep efficiency, sleep disturbance, use of sleeping medication, and daytime dysfunction.

5 Sheehan Disability Index (SDI)

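### HDRS is the only measure of depressive symptoms, yet it also scores insomnia, and no score without the sleep items is defined, so a sleep-only effect could be read as an effect on other residual symptoms

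*Protocol*

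**What the plan says.** The synopsis objective is efficacy and safety for "residual insomnia and other residual symptoms associated with major depressive disorder", which names insomnia and the remaining symptoms as separate targets. The synopsis section on clinical efficacy variables lists depressive state, measured by HDRS, among the primary outcomes.

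The Outcome Assessment section describes the instrument: "HDRS is a 21-item scale which the clinicians used to rate the severity of patients’ depression". The next sentence gives its content: "HDRS rates the severity of other depressive symptoms such as low mood, insomnia, agitation, anxiety and weight-loss". Insomnia is thus listed among the symptoms that the scale rates.

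Under Subjects, the trial takes outpatients "with a previous DSM-IV MDD and a chief complaint of insomnia" and excludes those who "have a Hamilton Depression Rating Scale scores above 18".

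Data Management and Analysis applies paired t-tests and a baseline-adjusted ANCOVA to the outcome measures in general. It has no separate rule for HDRS. Table 1 lists HDRS as a single entry at every visit. The protocol mentions no subscale, item-reduced score or sensitivity analysis.

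**The concern.** The other efficacy instruments do not cover mood. ISI, the sleep log, PSQI and actigraphy measure sleep, and SDI measures functioning. The second half of the objective therefore rests on HDRS alone, and HDRS contains the symptom that the first half is about.

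If acupuncture improves sleep only, the sleep items fall and the HDRS score falls with them. The trial would then show an HDRS difference that repeats the sleep finding, and nothing in the planned analysis would separate this from a change in low mood, anxiety or agitation. At stake is whether the trial can answer the question about other residual symptoms. The population makes the overlap more relevant: everyone enters with an insomnia complaint, while the overall HDRS score is capped.

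**Working it through.** **1. The overlap, from the text.** The objective separates insomnia from the other symptoms, HDRS is the only instrument for the latter, HDRS rates insomnia, and no reduced score is defined. The protocol never uses the word total for HDRS. It does name the 21-item scale as the measure of depressive state and offers no other score, so the full score is the plain reading.

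Write the between-group difference on the full score as

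difference(full) = difference(sleep items) + difference(all other items).

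For a sleep-only effect of s points the second term is zero, so difference(full) = s. The direction needs no assumption.

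**2. The plan's own figure.** The protocol sizes the trial on ISI, not HDRS. Inputs from Sample size estimation: SDs 4.7 and 3.6, correlation 0.5, difference 3, alpha 0.05 (two-sided reproduces the figure), power 80%.

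- n = (4.7² + 3.6²) × (1.960 + 0.842)² / 3² × (1 − 0.5²) = 30.57 × 0.75 = 22.93, so 23 per group, as stated.
- With 20% attrition: 23 / 0.8 = 28.75, so 29, in line with the stated figure of around 30.

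The sample size is sound and is not at issue. It supplies the 30 per arm used below.

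**3. How large could the HDRS signal be? Illustration only.** Not in the protocol and therefore assumed: HDRS SD of 4 to 6, and a sleep-item difference s of 1 or 2 points. For the adjusted case, the correlation of 0.5 is borrowed from ISI.

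- Unadjusted: d = s / SD.
- ANCOVA: d = s / (SD × √(1 − 0.5²)) = s / (0.866 × SD).
- Noncentrality = d × √(30/2) = 3.873 × d, compared with a two-sided 5% critical t of 2.002 on 58 degrees of freedom.

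| Sleep-only difference | HDRS SD | Unadjusted d | P(significant), t-test | P(significant), ANCOVA |
|---|---|---|---|---|
| 1 point | 6 | 0.17 | 10% | 11% |
| 1 point | 4 | 0.25 | 16% | 20% |
| 2 points | 6 | 0.33 | 25% | 31% |
| 2 points | 4 | 0.50 | 48% | 59% |

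With 24 per arm (30 × 0.8) and ANCOVA, a normal approximation gives 10-17% for 1 point and 27-52% for 2 points, so the picture is similar if dropouts are not analysed.

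**4. The same scenario with the sleep items removed.** The difference on the reduced score is the second term in step 1, which is zero. The chance of a significant result returns to 5%.

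**The case against.** The strongest reply is that insomnia belongs in a depression score. The Introduction defines residual symptoms as unresolved core depressive symptoms and counts insomnia among them, and the synopsis labels the outcome depressive state. A fall in HDRS is then a real fall in what the scale measures. This stands. It means that the percentages above are not type I error. A reader might infer that the plan carries a false-positive rate of 25-48% in place of 5%, but the null hypothesis for the full score is false once the sleep items move. The fault lies in what the result would be taken to show.

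Second, the number and weight of the sleep items, the HDRS SD and the likely sleep-item change are all absent from the protocol. This stands too. A reader might infer from the entry limit of 18 that sleep items make up a large share of the score. That is plausible in patients selected for insomnia, but no baseline HDRS data are given, and the 1-point case shows how modest the signal could be.

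Third, score derivation is often left to a statistical analysis plan, which is not shown here and might define a reduced score. That is possible. However, the choice of measure for a stated objective is made in the protocol, and as written that measure mixes the objective's two halves.

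Fourth, the consequence is limited. ISI is singled out as the primary measure in Outcome Assessment and in Sample size estimation, and the Aims section mentions only insomnia. This stands and bounds the point.

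A reader might also infer that HDRS is scored by someone who knows the arm. The protocol does not identify the rater, and rater blinding would affect the score with or without sleep items. It is a separate question on which nothing here depends.

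**Conclusion.** The point holds as a limit on interpretation. As written, the protocol cannot separate an effect on other residual symptoms from the sleep effect, because its only measure of the former includes the latter. The direction follows from the protocol's own description of HDRS.

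The size does not. Under an assumed SD of 4 to 6 and 30 per arm, a sleep-only difference of 1 to 2 points gives roughly a 10-48% chance of a significant HDRS result unadjusted. Under ANCOVA with the borrowed correlation of 0.5 it is roughly 11-59%. The documents do not support reading these as error rates, or as evidence that sleep items dominate the score. The ISI result and the sample size are untouched. This is a worthwhile, inexpensive improvement and not a threat to the trial's main conclusion.

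**What to change.** In the HDRS entry under Outcome Assessment, define a second score: HDRS without its insomnia items, with the omitted items named. In Data Management and Analysis, state that this score is analysed by the same baseline-adjusted ANCOVA and is the basis for any claim about other residual symptoms. Report the full HDRS score beside it. The full score need not be demoted to a descriptive role, and its use for eligibility does not change. Make the choice before outcome data are seen, since a later choice between the two scores would be open to selection.

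The cost is re-scoring items that are already rated, with no new visit or assessment. The downside is that the reduced score compares less directly with published totals, which is why both should be shown.

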Medications that are used to treat insomnia are limited by adverse effects, abuse and dependence. Psychological treatments are time intensive and require significant training for effective implementation. Pharmacological and psychological treatments of MDD have similar limitations. Acupuncture is one of the safest complementary therapies and has been used to treat insomnia and depression.10,11 Our previous randomized placebo-controlled study has shown that electroacupuncture is effective for primary insomnia.12

We aim to extend the use of acupuncture for treating residual insomnia associated with MDD. The reason for choosing this patient population is that the currently available pharmacological and psychological treatments have their limitations and may not be effective. In addition, the outcome and functioning of partially remitted depressed patients would be enhanced with remission of the residual symptoms.

We have conducted a pilot study comparing the efficacy of electroacupuncture, minimal acupuncture and placebo acupuncture for the treatment of residual insomnia in 30 subjects with MDD. We found that the subjects in electroacupuncture and minimal acupuncture groups had significantly greater improvement in Insomnia Severity Index (ISI) and Pittsburgh Sleep Quality Index (PSQI) scores at 4-week posttreatment than those in placebo acupuncture group (ANCOVA, ISI: F = 5.33, p = 0.01; PSQI: F = 7.93, p = 0.002). In view of the initial positive findings, it is important to extend the study for a longer follow-up period, in a larger sample and using objective outcome measure.

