Baseline differences between the electroacupuncture, minimal and placebo acupuncture groups would be examined using unpaired t-test or χ2 test. The last observation carried forward method would be used to handle missing data. The outcome measures during acupuncture treatment and at posttreatment would be compared with that at baseline using paired t-test. A 2 × 3 (time × group) ANCOVA with baseline measure as a covariate would be used to investigate differences between the electroacupuncture, minimal and placebo acupuncture groups. Standardized effect size would be computed by dividing the difference in means by the pooled standard deviation to estimate treatment impact. The clinical significance of the interventions would be estimated by the proportion of participants who reached sleep-diary SOL or WASO of 30 minutes or less and SE of at least 85%, and χ2 or Fisher exact test would be used to test for group differences.

Safety analyses

Subjects who receive at least 1 acupuncture treatment will be included for safety analyses. Adverse events will be coded using the WHO Adverse Reaction Terminology Dictionary. Special attention will be given to those subjects who have discontinued treatment due to an adverse event or who experience a severe or serious adverse event.

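### The baseline comparison and the efficacy ANCOVA name a minimal-acupuncture arm that this trial does not randomise and omit the waiting-list arm that it does

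*Protocol*

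**What the plan says.** Under Study Design, the protocol states: "Eligible patients will be randomized in a ratio of 1:1:1 to: (1) traditional electroacupuncture; (2) placebo acupuncture using Streitberger needle; and (3) waiting list control". On the third arm it adds: "Patients in the waiting list control group will not receive any treatment for a period of 8 weeks after randomization". After that, this arm receives the electroacupuncture treatment. The same section lists three explanations for improvement that the design is meant to tell apart. The third is "underlying fluctuations in the disorder, regression to the mean, or non-specific improvement associated with participating in a clinical trial".

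Under Data Management and Analysis, two sentences name groups:

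- On baseline: "Baseline differences between the electroacupuncture, minimal and placebo acupuncture groups would be examined using unpaired t-test" or a χ2 test.
- On efficacy: a time-by-group ANCOVA with three group levels and the baseline value as covariate "would be used to investigate differences between the electroacupuncture, minimal and placebo acupuncture groups".

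The waiting list is not mentioned in that section. The Introduction shows where a minimal arm did exist: a pilot "comparing the efficacy of electroacupuncture, minimal acupuncture and placebo acupuncture for the treatment of residual insomnia in 30 subjects" with MDD.

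Under Method of randomization, subjects are allocated to one of three groups. Under Method of blinding, the script tells them: "You will be randomly assigned to traditional acupuncture group for insomnia or acupuncture-like placebo treatment group".

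**The concern.** The group list in the analysis section does not match the arms that are randomised. Taken literally, the ANCOVA has one group level with no patients, and one randomised arm has no level.

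The waiting list is the only arm that shows what happens without needling or imitation needling. It is therefore the only arm that can isolate the third explanation in Study Design. If no comparison with it is named, those contrasts would have to be chosen later, possibly after data have been seen, and could not be presented as prespecified in this protocol.

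This is not detail that a protocol leaves to an SAP. The protocol fixes the groups and fixes them wrongly, so an SAP that named the correct arms would contradict it.

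**Working it through.** **1. Arms against analyses**

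| Group | Randomised (Study Design) | Procedure described (Treatment Protocol) | Baseline comparison | ANCOVA |
|---|---|---|---|---|
| Electroacupuncture | yes | yes | named | named |
| Placebo (Streitberger) | yes | yes | named | named |
| Waiting list | yes | not needed for 8 weeks | not named | not named |
| Minimal acupuncture | no (pilot only) | no | named | named |

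**2. The other analyses in the same section**

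- Paired t-tests against baseline: these are within-group and timed by acupuncture treatment. They do not compare arms and cannot separate regression to the mean from a treatment effect.
- Standardised effect size: no groups named.
- Responder proportion by χ2 or Fisher exact test: refers to group differences without naming the groups.

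The waiting list is thus in neither analysis that names groups. The last two are open enough to include it.

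**3. Share of patients**

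- Sample size estimation: 90 / 3 = 30, and 30 / 90 = 33.3%.
- Synopsis: 96 / 3 = 32, and 32 / 96 = 33.3%.

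The difference between 90 and 96 is a separate discrepancy and does not alter the share.

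**4. Contrasts**

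Three randomised arms give three pairwise contrasts. The ANCOVA's list also gives three pairs, but two involve minimal acupuncture and so have no patients on one side. Only electroacupuncture versus placebo is on both lists: 1 of 3.

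**5. Whether the correction changes the sample size**

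Inputs from Sample size estimation: SDs 4.7 and 3.6, ρ = 0.5, Δ = 3, α = 0.05, power 80%. Sidedness is not stated.

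n = (SD1² + SD2²)(z_α + z_β)² / Δ² × (1 − ρ²)

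- Two-sided: (22.09 + 12.96) × (1.960 + 0.842)² / 9 = 30.57, and 30.57 × 0.75 = 22.93, so 23. This matches the protocol.
- One-sided: 24.08 × 0.75 = 18.06, so 19. This does not match.
- Attrition of 20%: 23 / 0.8 = 28.75, so 29, consistent with the planned figure of around 30.

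The calculation is for a two-group comparison, so naming the right arms leaves it unchanged. With 23 evaluable patients per arm, a comparison with the waiting list would have 80.1% power at two-sided 0.05, assuming the pilot SDs, ρ and a 3-point difference also hold for that comparison.

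**6. Which visits can be compared with the waiting list**

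Eight weeks is 56 days after randomisation. Taking Table 1 days as days from randomisation (an assumption):

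- D15–D21 ± 2 covers D13 to D23: inside the untreated period.
- D29 ± 2 covers D27 to D31: inside.
- D57 ± 4 covers D53 to D61: straddles the end at day 56.
- D113 ± 4 covers D109 to D117: after this arm is due to receive electroacupuncture.

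**The case against.** The strongest reply is that nobody would run the analysis literally. The ANCOVA has three group levels, the trial has three arms, and no minimal-acupuncture procedure is described. The list looks like wording carried over from the pilot. In addition, the Aims concern the efficacy and safety of electroacupuncture, and electroacupuncture versus placebo is named and testable. Most of this stands. The carry-over reading is an inference, but a likely one, and the main treatment comparison is not lost. It does not rescue the text, because the same wrong list appears twice and the third purpose in Study Design still has no named test.

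A reader might infer that a third of the patients enter no efficacy test at all. The protocol does not support that: the responder test and the effect-size sentence name no groups and could take in the waiting list.

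A reader might also infer from the script that subjects were told there was no waiting list, with extra dropout or disappointed ISI ratings to follow. The script omits that arm but does not deny it. Consent pages are not in the copy reviewed and may name it. No figure in the protocol supports an effect on dropout or ratings, and Study Design offers this arm electroacupuncture after the wait.

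**Conclusion.** The contradiction is real and should be corrected before the analysis is relied on. Both sentences that name groups list an arm that does not exist in this trial and leave out one that does. The omitted arm is 33.3% of randomised patients on either stated total. It has no named between-group test of the ISI, and two of the three contrasts between real arms are not named. The planned sample size is not affected.

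The conclusion is limited to the baseline comparison and the ANCOVA, and rests on reading their group lists as written. The mismatch between the two-group script and the three-group randomisation is a separate internal contradiction about what subjects are told.

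**What to change.** 1. In both sentences, replace the group list with: electroacupuncture, placebo acupuncture and waiting-list groups.
2. For continuous baseline variables, replace the unpaired t-test with a three-group test, or state which pairwise tests are meant. An unpaired t-test does not fit three groups.
3. State the contrasts: electroacupuncture versus placebo, electroacupuncture versus waiting list, and placebo versus waiting list. Their ranking can be left to the SAP.
4. Limit waiting-list contrasts to assessments made before that arm starts treatment. The visits up to D29 qualify. D57 qualifies only where the visit precedes the first treatment. D113 does not.
5. Say whether the responder test and the effect sizes cover all three arms.
6. Separately, reconcile the script under Method of blinding with the three-group allocation under Method of randomization.

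Items 1 to 5 are text amendments and need no additional patients. For the D57 rule, the date of the first treatment in the waiting-list arm must be on record. Item 6 is also a change of text, but it may alter what subjects are told about their allocation and should be handled as such.

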**Introduction**

Major depressive disorder (MDD) is a debilitating illness that affects an estimated 13% of the general population.1 It was the fourth leading cause of disability and disease, accounting for 4.4% of the total disability-adjusted life years in the year 2000.2 Residual symptoms in MDD can be defined as core depressive symptoms that have not resolved with treatment.3 Insomnia is one of the most common residual symptoms associated with MDD.

Previous studies have shown that residual symptoms associated with MDD are common. Approximately one third of patients with MDD fail to fully respond to antidepressant treatment of adequate dose and duration.4 In one study, Nierenberg et al. investigated 108 depressed patients who had received an 8-week treatment of fluoxetine, an antidepressant.5 They found that the prevalence of residual insomnia was 44%, followed by fatigue (38%) and diminished interest (27%). Nelson et al. showed that the prevalence of different subtypes of residual insomnia was: difficulty initiating asleep (37%), midnight awakening (33%), and early morning awakening (20%).6

Effective treatment of residual symptoms is essential, since their persistence correlates with a greater risk of MDD recurrence and relapse as well as worse psychosocial functioning. Tranter et al. found that depressed patients with residual symptoms had a relapse rate 3-6 times higher than in those who experienced full remission.7 In another study, Mojtabai et al. found that the severity of residual symptoms was associated with the number of days of impaired occupational functioning.8

Residual insomnia can be a symptom of MDD that requires longer time to remit, a side effect of pharmacological treatment, or a feature etiologically different from but coexist with MDD.3 In a study that compared the rate of residual insomnia following pharmacotherapy or cognitive behavioral therapy for MDD. Carney et al. found that the rate of residual insomnia after drug and non-drug treatment was 53% and 50%, respectively, suggesting that medications alone cannot account for the residual insomnia symptoms.9

There have been limited studies examining the treatment of residual insomnia in MDD. One approach is to treat residual insomnia by augmentation of antidepressant treatment using drug and non-drug approaches. On the other hand, pharmacological or psychological treatments targeting insomnia symptoms may enhance the recovery of both sleep and mood disturbance.

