SDI is a 3-item self-rating scale that assesses the subjects’ functioning regarding work/study, social life and family.

Objective assessment

Actigraph

Actigraph is a watch-like device used to estimate sleep-wake schedules by measurement of activity. The subjects are asked to wear the actigraph on the dominant wrists prior to light off for 3 consecutive nights. Subjects will be told to have usual bedtime when they are measured by actigraph.

Assessment for safety

Reason for withdrawal

When a subject withdraws before completing the study, the reason for withdrawal will be recorded.

Adverse events

Adverse events will be assessed at each visit. The researcher will ask using open-ended questions whether the subjects experience any adverse events during the assessment visit.

Assessment for credibility

Credibility of treatment rating scale (modified by C Vincent) will be used to assess the credibility of the treatments.17 The 4-item scale is specially designed to assess the credibility of acupuncture.

*Data Analysis*

Sample size estimation

Insomnia Severity Index (ISI) is selected as the primary outcome measure. The sample size estimation is based on our pilot study. We found that the SD of ISI score in the treatment and control group was 4.7 and 3.6, respectively, while the baseline and endpoint ISI score correlation coefficient was roughly 0.5. Vickers and Altman proposed that analysis of covariance (ANCOVA) was the preferred approach to analyse controlled trials with baseline and follow up measurements.18 We estimate the sample size requirement per treatment group using:

(1- ρ2)

An adjustment factor (1- ρ2) is used to determine the sample size in each group;19 and ρ is the baseline and endpoint measure correlation coefficient.

Let type I error a = 0.05; type II error β = 0.20; and power (1-β) = 80%. The SD δ1= 4.7, δ2 = 3.6 and ρ = 0.5. A clinically significant treatment effect is taken as a 3 ISI point between-group difference (Δ = 3). Therefore, a sample size of 23 is needed in each group. We estimate a 20% attrition rate; hence a sample size of around 30 in each group (90 in total) is planned for this study.

Data Management and Analysis

All data are double-entered and checked for consistency prior to analysis.

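### The supportive clinical-significance rule is unbracketed, comes close to a sleep-efficiency cut-off alone, and takes no account of baseline status

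*Protocol*

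**What the plan says.** Protocol, Data Analysis, Data Management and Analysis: clinical significance is "estimated by the proportion of participants who reached sleep-diary SOL or WASO" within the stated limits. The criterion in full is "sleep-diary SOL or WASO of 30 minutes or less and SE of at least 85" per cent. SOL and WASO are joined by *or*, SE is added by *and*, and there are no brackets. For the comparison, "χ2 or Fisher exact test would be used to test for group differences". No baseline condition is given, although the same paragraph uses the baseline measure as a covariate in the ANCOVA.

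Protocol, Subjects: patients enter "with a previous DSM-IV MDD and a chief complaint of insomnia". Neither the inclusion nor the exclusion criteria set a minimum ISI, SOL or WASO, or a maximum SE.

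Protocol, Introduction: difficulty falling asleep (37%), waking in the night (33%) and early waking (20%) are listed as separate forms of residual insomnia, from one cited study.

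Protocol, Table 1: a one-week sleep log is collected at baseline and at every later visit. Method of randomization places allocation after the baseline visit.

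**The concern.** A rule with three conditions suggests that a success sleeps well on all three. With *or*, one of the two 30-minute limits is enough. A patient whose only problem is night waking can satisfy that part through SOL, which was never abnormal; a patient whose only problem is falling asleep can satisfy it through WASO. What then decides the outcome is SE.

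Secondly, the rule counts where patients end up, not whether they moved. A complaint of insomnia does not guarantee a sleep log outside the limits, and Concomitant Therapy allows hypnotics during the study. Anyone inside the limits at baseline who stays there is counted as a success in whichever arm they fall.

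At stake is the meaning of the one patient-level measure of clinical significance in the analysis section, and the sensitivity of its between-group test. The ISI analysis is not at stake.

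**Working it through.** **The plan's own figure.** The protocol gives no number for this rule. Its only computed figure is the ISI sample size, from SDs 4.7 and 3.6, ρ = 0.5, Δ = 3, α = 0.05 (two-sided assumed) and 80% power:

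n = (1.960 + 0.842)² × (4.7² + 3.6²) / 3² × (1 − 0.5²) = 30.57 × 0.75 = 22.93, so 23 per group. With 20% attrition, 23 / 0.8 = 28.75, so 29, against the planned figure of around 30. It reproduces, and nothing below alters it.

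**Inputs for the rule.** From the protocol: 30 minutes, 85%, *or*, *and*. Assumed, because the protocol gives neither: time in bed (TIB) of 6 to 9 hours, and SE = 1 − (SOL + WASO) / TIB with no other wake time.

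**Step 1: what SE alone allows.** SE ≥ 85% means SOL + WASO ≤ 0.15 × TIB.

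| TIB | Limit on SOL + WASO | Largest WASO that passes with SOL 10 |
|---|---|---|
| 6 h | 54 min | 44 min |
| 7 h | 63 min | 53 min |
| 8 h | 72 min | 62 min |
| 9 h | 81 min | 71 min |

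**Step 2: what the 30-minute part adds.** To fail it, a patient needs SOL > 30 and WASO > 30, hence a sum above 60. SE already rules that out when 0.15 × TIB ≤ 60, that is TIB ≤ 400 min, or 6 h 40 min. Up to that point the 30-minute part excludes nobody. At 8 hours it excludes only pairs with both values above 30 and a sum of at most 72.

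**Step 3: individual cases at 8 hours (480 min).**

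| SOL / WASO | SE | Rule as naturally read | Both ≤ 30 and SE ≥ 85% |
|---|---|---|---|
| 5 / 65 | 410/480 = 85.4% | success | failure |
| 60 / 10 | 410/480 = 85.4% | success | failure |
| 15 / 25 | 440/480 = 91.7% | success | success |
| 10 / 120 | 350/480 = 72.9% | failure | failure |

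In the first two rows one parameter is at least twice the rule's own limit (65/30 = 2.2; 60/30 = 2.0).

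**Step 4: the missing brackets.** The words can also be parsed as SOL ≤ 30, or else WASO ≤ 30 together with SE ≥ 85%. Under that parse the last row (10 / 120) becomes a success.

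**Step 5: baseline status.** Let a share b meet the rule at baseline and stay there, and let the rest respond at p1 and p0. The observed rates are b + (1 − b)p1 and b + (1 − b)p0, so the difference is (1 − b)(p1 − p0). Power below is the normal approximation for two proportions, two-sided 0.05, 30 per group, two arms compared. The values of b, p1 and p0 are assumptions.

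| p1 v p0 | b | Observed rates | Difference | Power, all patients | Power, baseline passers excluded, 30(1 − b) per group |
|---|---|---|---|---|---|
| 50% v 20% | 0 | 50% v 20% | 30 points | 69.2% | 69.2% |
| 50% v 20% | 0.2 | 60% v 36% | 24 points | 45.9% | 59.1% |
| 50% v 20% | 0.4 | 70% v 52% | 18 points | 29.5% | 46.9% |
| 40% v 15% | 0 | 40% v 15% | 25 points | 58.6% | 58.6% |
| 40% v 15% | 0.2 | 52% v 32% | 20 points | 34.5% | 49.2% |
| 40% v 15% | 0.4 | 64% v 49% | 15 points | 21.3% | 38.5% |

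The table models baseline status only. It says nothing about the effect on power of replacing *or* by *and*.

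**The case against.** The strongest reply is that the SE condition is a real safeguard, and that stands. A reader might infer from the *or* that patients with untreated maintenance insomnia generally count as successes. On the natural reading they do not: at 8 hours in bed with SOL 10, any WASO above 62 minutes fails. Only mild to moderate cases get through.

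A reader might also infer that many enrolled patients already sleep within the limits. The documents do not show this. Insomnia must be the chief complaint, the baseline share is not given, and the word *reached* may have been meant as a change, though it is not defined so. Nor do the subtype percentages in the Introduction show how many patients have only one problem, since no overlap is reported.

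Nor do the documents support reading this as bias toward an arm. Randomisation balances baseline passers in expectation, so the effect is higher rates everywhere and a smaller contrast.

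It is also fair that the analysis is supportive, that requiring both limits is not the only possible repair (one could require improvement in whichever parameter was abnormal at baseline), and that a stricter rule need not raise power. Finally, denominators and visits for a supportive proportion are often left to an analysis plan, which may exist here. That last point does not dispose of the matter: the cut-offs, the connective and the unadjusted test are fixed in the protocol itself, and as fixed they pass patients who are well outside one of the 30-minute limits.

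**Conclusion.** The concern holds in a limited form. The rule needs brackets and, on its natural reading, is nearly the same as SE of at least 85%: the 30-minute part is inactive up to 6 h 40 min in bed and excludes few combinations at 8 hours. A success can therefore have WASO of 65 minutes or SOL of 60. This rests on an assumed time in bed and on no wake time outside SOL and WASO; if early-morning wake time is counted separately, the allowance for SOL + WASO is smaller still and the 30-minute part has even less to do.

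The lack of a baseline condition dilutes the comparison to the extent that patients already meet the rule. With 20% to 40% doing so, a true 30-point difference would appear as 24 to 18 points; these shares and response rates are illustrations. How many patients would be misclassified cannot be derived from the protocol. The change should be made, but it concerns a supportive analysis. The ISI analysis and its 23 (around 30) per group are unaffected.

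**What to change.** Define success on the one-week sleep log as (SOL ≤ 30 minutes and WASO ≤ 30 minutes) and SE ≥ 85%. Compare it among patients who do not meet it at baseline, or adjust for baseline status, and report by arm how many met it at baseline. Because the baseline log precedes allocation, restricting the comparison in this way does not break the randomised contrast.

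The change takes a sentence or two and no new data. It should be settled before the data are unblinded. The cost is lower responder proportions and a smaller denominator: with b = 0.2, for example, 24 rather than 30 per group. The planned sample size stays as it is.
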